### Participant timeline {13}

Figure 1 provides an overview of the trial schedule, including details on enrolment, interventions, and assessment timelines.

**Fig. 1 Fig1:**
[figure not shown]
Trial schedule *Note. T*_*1*_,* T*_*2*_,* T*_*3*_,* T*_*4*_ time points; *AFQ-Y* Avoidance and Fusion Questionnaire for Youth; *MAYSI-2* Massachusetts Youth Screening Instrument-2; *CD-RISC* Connor-Davidson Resilience Scale; *WHO-5* World Health Organization – Five Well-Being Index; *CIS* Columbia Impairment Scale; *PHQ-4* Patient Health Questionnaire-4; *SWE* Skala zur Allgemeinen Selbstwirksamkeitserwartung [General Self-Efficacy Expectancy Scale]; *CSQ* Client Satisfaction Questionnaire; *ARI* Affective Reactivity Index; *EssenCES* Essen Climate Evaluation Schema; *TSQ* Trainer Satisfaction Questionnaire*.* Data will be collected at screening (T_0_), ≤ 4 (+ 2) weeks before the intervention (T_1_; baseline assessment), ≤ 2 weeks after the intervention has ended (T_2_; post-intervention assessment), 12 ± 2 weeks post intervention (T_3_; first follow-up), and 24 ± 2 weeks post intervention (T_4_; second follow-up)

### Sample size {14}

The sample size estimation was performed in statistical software R using a simulation-based approach. The sample size estimation is based on the assumptions, that standard deviations of AFQ-Y scores are equal for all groups and conditions, and that the mean baseline scores of all groups are equal due to randomization. We assumed the AFQ-Y scores at baseline to be normally distributed with a mean of 21.04 and standard deviation of 13.01 [37]. Further, we assumed a high correlation of AFQ-Y scores within participants between time-points, with a Pearson correlation coefficient of *r* ~ = ~ 0.80. The effect sizes of the intervention in standardized Cohen’s *d scores were* = -.50 for TAU vs. web-based self-help training and Cohen's *d* = -.80 for TAU vs. web-based group training.

The above assumptions regarding distribution, correlations, and effect sizes were used to determine the required sample size with a simulation-based approach. Based on the above assumptions and distributions, 9999 synthetic data sets of different sample sizes were generated. The primary analysis was applied to each of these data sets. The simulations showed that at an effective sample of *N* = 78 (26 participants per condition) would enable us to reject the null hypothesis with the desired power of 80%.

In the next step, we corrected this sample size for the design effect (i.e., clustering of participants in groups), assuming a weak resemblance in the AFQ-Y score of patients within the same group (rho = 0.2) [53]. Before the start of the study, we assumed a group size (i.e., participants receiving the intervention together) of on average 9 participants. During a sample size re-estimation, this number was reduced to 4 participants per group as was observed in the study centers. With an estimated drop-out rate of 20% [17], 150 patients (i.e., 50 patients per condition) must be recruited to reject our null hypothesis at a power of 80% considering the effect of clustering. The expected flow of participants from recruitment through the end of the study is shown in Fig. 2.

**Fig. 2 Fig2:**
[figure not shown]
Trial flowchart *Note. TAU* treatment as usual

### Recruitment {15}

All institutions recognized by the FOJ will be informed about the study through mail, phone, and announcements by the study team in Basel. Interested and eligible institutions will be provided with recruitment material. Potential participants will be linked to the START NOW Basel study team and received all information about the study during a video call: nature of the study, its purpose, the procedures involved, the expected duration, and potential risks and benefits. Each potential participant will be informed that the participation in the study is voluntary and that he or she may withdraw from the study at any time and that withdrawal of consent will not affect his or her subsequent treatment. Study information and informed consent forms will be provided to all participating institutions.

To ensure thorough recruitment, all recognized institutions will be contacted via various channels, including mail, phone, and personal contact. The trial systematically addresses all eligible participants within the designated timeframe, with ongoing communication efforts. Adolescent participants will receive compensation and retained WebApp access throughout, with TAU participants gaining access post follow-up II. Participating institutions will receive training in START NOW, open to interested staff, and institution in the TAU condition will receive training and WebApp access after follow-up II.

### Assignment of interventions: allocation {16}

#### Sequence generation {16a}

The randomization process will occur at the institutional level when a minimum of four eligible participants were available (gave informed consent and passed screening). Participants will be randomized within fully eligible groups of 4 to 12 individuals, stratified by study site and across 3 conditions. Institutions will be randomized using a pre-generated list, generated using the statistical software R, inaccessible to the research team, and provided and implemented through the DCR at the University of Basel.

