### Trial design {8}

The study is a monocentric, prospective, confirmatory randomized controlled trial with three experimental conditions: (1) START NOW as web-based group training guided by a facilitator, (2) START NOW as web-based pure self-help training, and (3) TAU. Institutions are randomly assigned 2 weeks before the 9-week intervention phase.

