#### Implementation {16c}

Institutional randomization will occur after obtaining consent from at least four eligible participants within an institution. The process will be initiated using a pre-generated list attached to REDCap, which is not visible to the study team. The allocation sequence is generated by the DCR.

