### Oversight and monitoring {21}

#### Composition of the coordinating center and trial steering committee {5d}

This is a monocentric study, planned, coordinated, and conducted by the START NOW team of the Child and Adolescent Psychiatric Research Department at the University Psychiatric Clinics Basel. The Principal Investigator oversees the study’s implementation, carried out by the study coordinator and a study team. The study team recruits, obtains informed consent, and ensures the protocol’s compliance in accompanying participating institutions and AYA. The study team holds weekly meetings. The sponsor receives biannual updates on the current status of the study. There is no steering committee or other involved parties.

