## Discussion

This randomized controlled trial aims to investigate the efficacy of a web-based translation of START NOW, promoting PF in institutionalized AYA and addressing implementation barriers in RYC and CI. Within participating institutions, 150 AYA with a need to improve resilience will be randomly assigned at the institution level to one of three conditions (i) a 9-week web-based group training guided by a facilitator, (ii) a 9-week web-based self-help training, and (iii) TAU.

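### Sequence generation {16a} contradicts the institution-level allocation stated elsewhere and names an undefined stratum; the models should be tied to the unit, and any stratum, actually used

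*Protocol article*

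**What the plan says.** Three consecutive statements in Sequence generation {16a} deal with the unit of randomisation.

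- The first names the institution: "The randomization process will occur at the institutional level when a minimum of four eligible participants were available".
- The second names participants and adds a stratification factor: "Participants will be randomized within fully eligible groups of 4 to 12 individuals, stratified by study site and across 3 conditions".
- The third goes back to the institution as the unit: "Institutions will be randomized using a pre-generated list, generated using the statistical software R, inaccessible to the research team".

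Elsewhere the institution is always the unit. Trial design {8}: "Institutions are randomly assigned 2 weeks before the 9-week intervention phase". Implementation {16c}: "Institutional randomization will occur after obtaining consent from at least four eligible participants within an institution". Discussion: "randomly assigned at the institution level to one of three conditions". The title calls the trial cluster randomised, and the abstract says that institutions are randomised. The September 2022 entry in the amendment section {25} lets a large institution run more than one group, at the same time or in sequence, provided that all are in the same condition.

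On centres, the section on the coordinating centre {5d} says "This is a monocentric study", and Trial design {8} agrees.

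The primary model in Statistical methods {20a} has fixed effects for intervention and baseline AFQ-Y and one random intercept. That intercept is for the institution group, which the text explains by reference to training groups inside institutions. For the secondary endpoints, the same section defines the group as the training group within the institution. Neither model has a stratum term.

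**The concern.** Sequence generation is the item that has to fix the unit of randomisation and any stratification. As it stands, it gives two units and one factor that cannot be identified.

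Both matter for the analysis. The randomised unit decides where the random effect must sit and what the treatment contrast is compared with. If institutions are randomised but the only random intercept is for a smaller unit, variation between institutions is treated as if it averaged out over more independent units than there are, and standard errors come out too small. If the list was stratified by a real factor that the model omits, the error usually goes the other way: standard errors tend to be too large. The documents do not allow the size of that second effect to be worked out.

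**Working it through.** **1. Can the sentence be reconciled with the rest?**

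- *Individuals randomised inside each group.* This contradicts the sentences before and after it, and sections {8}, {16c} and the Discussion.
- *Whole groups allocated, stratified by site.* If site means institution, stratifying would spread the groups of one institution over the conditions. The amendment section {25} requires the opposite.

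**2. What could study site mean?**

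- *The centre.* The trial is monocentric, so the factor has one level and stratifies nothing.
- *The institution.* Sample size {14} speaks of study centres where it means the places in which groups of 4 were observed, so this reading is plausible. But the institution is the randomised unit and receives one condition, so conditions cannot be balanced within it.
- *Something else.* The documents name no other stratification factor.

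**3. Which unit does the sample size assume?** Inputs from Sample size {14}: effective N 78, group size 4, ICC 0.2, dropout 20%.

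- Design effect: 1 + (4 − 1) × 0.2 = 1.6
- 78 × 1.6 = 124.8
- 124.8 × 1.2 = 149.8, rounded up to 150, the stated total

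The stated 150 therefore already contains a design effect for clusters of 4. It follows the cluster reading and not the sentence in {16a}.

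**4. When does the primary model fit the allocation?** With one training group per institution, group and institution coincide. If there is also no real stratum, the model matches. With k groups of 4 in an institution, all in one condition, let s be the share of the ICC of 0.2 that lies at institution level.

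- Design effect seen by a group-only intercept: 1 + 3 × 0.2 = 1.6
- Design effect for institution-level allocation: 1.6 + (k − 1) × 4 × 0.2 × s
- Approximate two-sided type I error at nominal 0.05: 2 × [1 − Φ(1.96 × √(1.6 / institution-level design effect))]

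| k | s (assumed) | Institution-level design effect | Type I error |
|---|---|---|---|
| 1 | any | 1.6 | 0.050 |
| 2 | 25% | 1.8 | 0.065 |
| 2 | 50% | 2.0 | 0.080 |
| 2 | 100% | 2.4 | 0.110 |
| 3 | 25% | 2.0 | 0.080 |
| 3 | 50% | 2.4 | 0.110 |
| 3 | 100% | 3.2 | 0.166 |

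Example for k = 2, s = 50%: 1.96 × √(1.6 / 2.0) = 1.753, two-sided p = 0.080.

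This is a large-sample approximation. It assumes that every institution has the same k and that the group intercept absorbs the whole ICC. The documents give neither s nor the number of institutions with more than one group.

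**The case against.** The best defence is that the unit is not in real doubt. The title, the abstract, sections {8} and {16c}, the Discussion and the neighbouring sentences all say institution, and the sample size carries a design effect. The sentence can be taken as loose wording for participants who are randomised as members of an eligible group. That stands: the documents give no ground to infer that individuals really were randomised within groups.

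It is also fair that adjustment for a stratum is commonly left to the SAP, which is announced but not shown. The absence of a stratum term is therefore not a fault in itself. It matters only if a stratum was used.

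Two stronger readings do not hold. A reader might infer that the primary model is mismatched to the randomisation as a matter of fact. It has a cluster intercept, and a mismatch needs either a real stratum left out or several groups per institution with the intercept at group level. The second condition comes from sections {20a} and {25}, not from the sentence in {16a}. A reader might also infer that the contradiction makes the sample size wrong by the design effect of 1.6. It does not, because that factor is already in the 150.

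The defence does not rescue the stratification phrase, which has no workable meaning as written. Nor does it settle whether the intercept is for the institution or the training group.

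**Conclusion.** The concern holds in a limited form. The sentence in {16a} is wrong as written: it contradicts institution-level allocation, and its stratum is undefined and cannot be the centre or the institution.

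The effect on the analysis is conditional. With one group per institution and no real stratum there is none. With two groups of 4 per institution and a group-only intercept, the type I error is about 0.065 to 0.11 for institution-level shares of 25% to 100%. With three groups it is about 0.08 to 0.17. If only some institutions have several groups, the value should lie between 0.05 and these figures. The shares and the numbers of groups are assumptions. The ICC of 0.2 and the group size of 4 are the protocol's own.

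On its own the rewording would be clerical. The point earns its place because the level of the random effect and any stratum term bear on the standard errors of a confirmatory comparison.

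**What to change.** 1. Replace the sentence in {16a}. For example: *Whole institutions are allocated to one of the three conditions from the list generated in advance; every training group of an institution receives that institution's condition.*
2. From the list held by the Department of Clinical Research, report the allocation ratio for institutions, which the article does not give, and whether a stratification factor was used and which one. If there was none, delete the stratification.
3. In the primary and secondary models, place a random intercept at the institution, with training group nested within it where an institution has several groups. If a stratum was used, add it as a fixed effect.
4. Report how many institutions had more than one group, so that readers can see whether the nesting matters.

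Recruitment ended in July 2023 (Trial status), so allocation cannot change; the text and the analysis can. If the SAP already specifies this, only the article's wording needs correcting. The cost is one extra variance component and at most one fixed effect, with possibly wider confidence intervals. If few institutions have several groups, the nested variance may be poorly estimated, and the SAP should say that the institution intercept is then the one to keep.

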#### Concealment mechanism {16b}

The allocation sequence is solely handled by the Clinical Trial Unit of the DCR and is not accessible to the study team. Upon randomization, allocation will be revealed to the study team members via REDCap. Subsequently, the study team members will inform participating institutions and AYAsn.

#### Implementation {16c}

Institutional randomization will occur after obtaining consent from at least four eligible participants within an institution. The process will be initiated using a pre-generated list attached to REDCap, which is not visible to the study team. The allocation sequence is generated by the DCR.

### Assignment of interventions: blinding {17}

#### Who will be blinded {17a}

Not applicable. After randomization, the START NOW study team will inform the participating institution, and consequently, the participants, about their allocation to the respective condition.

#### Procedure for unblinding if needed {17b}

Not applicable, as the study design does not involve blinding.

### Data collection and management {18}

#### Plans for assessment and collection of outcomes {18a}

Data, including electronic Case Report Form (eCRF), will be collected using REDCap. Participants and caretakers will fill out questionnaires, while trained members of the study team will enter objective study data (time-points, participant data from consent form, etc.). Participants will be sent personalized links to the questionnaires at standardized time-points. Questionnaires can be completed on mobile and desktop devices with internet access. WebApp usage data will be collected automatically.

#### Plans to promote participant retention and complete follow-up {18b}

Participants are consistently reminded to complete the questionnaires. As compensation for completing all online questionnaires at survey times T_1_ to T_4_, all participants can receive shopping vouchers worth a maximum of CHF 100.-. For each missing T, CHF 20.- will be deducted from the total. The respective shopping vouchers will be handed out at the end of the participation period.

### Data management {19}

Trial data is stored in REDCap, including online questionnaire data and eCRF. Serious adverse events (SAE) will be recorded in the eCRF. The online platform REDCap is operated in compliance with 21 CFR Part 11 to ensure restricted access for qualified personnel, data security, incident, and change management. Forms validate all entries of the study team, participants, and caretakers. All changes are logged automatically with no option for the study team to manipulate the history.

Informed consent forms will be stored in paper within a locked cabinet in a secured room. WebApp usage data is stored in the WebApp and is only accessible to administrators. All members of the study team are instructed in-person and with videos, with all training sessions and permissions logged. Protocol violations will be recorded separately from study data and provided to the monitor.

### Confidentiality {27}

The principal investigator will maintain a subject ID list to enable records to be identified. The participant identification list will be stored in the Investigator Site File that is locked away in a fire-secure locker in a dedicated room in the research department of Child and Adolescent Psychiatry at UPK. Only authorized staff have access. Authorized personnel may inspect the subject-related data collected during the trial, ensuring compliance with the data protection law (inspectors, monitors, auditors). A back-up digital Excel file will be stored on a laptop with no internet access, located in a dedicated locked room. Only study investigators will have access to the passwords required to boot the laptop and open the Excel file.

All study data are archived for 10 years after study termination or premature termination of the study. Trial data will be archived at the Center for Scientific Computing of the University of Basel and WebApp entries will be archived at Arteria GmbH Basel. After these 10 years, all physical records will be destroyed and the document linking personal details and study codes will be deleted.

### Plans for collection, laboratory evaluation, and storage of biological specimens for genetic or molecular analysis in this trial/future use {33}

Not applicable as no biological specimens were used in this trial.

### Statistical methods {20}

#### Statistical methods for primary and secondary outcomes {20a}

A detailed statistical analysis plan will be written by the study statistician and kept under version control at the DCR. The statistical analysis plan will be finalized before the last visit of the last patient and the final version will be stored before access to the study database is granted.

All outcomes of interest will be described stratified by intervention group at each of the time-points of assessment by mean and standard deviation, median, or median and interquartile range, as appropriate. We will also visualize the time course of the endpoints of interest by intervention group.

The primary objective is to compare the follow-up AFQ-Y score (12 ± weeks after the end of the intervention) between the 3 intervention arms. To this end, we will perform an intention-to-treat analysis, analyzing all participants in the groups they were randomized to, regardless if they actually completed the particular intervention. We will use the imputed full analysis set for the primary analysis. The primary endpoint is the change in AFQ-Y score from baseline (T_1_) to the first post intervention follow-up (T_3_, 12 ± weeks). We will fit a linear mixed-effects model for the primary endpoint post intervention AFQ-Y score. The identifier of the institution group will be included as a random intercept to account for the clustered data structure (i.e., participants in training groups within institutions). The intervention (3 levels with TAU as reference) will be included as a fixed effect of interest, and the baseline AFQ-Y score is included in the model as a covariate. We will examine the distribution of the residuals to assess the model assumptions. The estimate of the fixed effect will be presented together with the corresponding 95% confidence interval and p-value. All analyses will be performed in R version 4.3.1 or higher.

Secondary endpoints involve assessing short-term and long-term intervention effects on diverse outcome measures. Short-term effects, immediately post intervention, will be analyzed using various scales, including CD-RISC, SWE, WHO-5, CIS, PHQ-4, and ARI. Long-term effects, at 12- and 24-week follow-up, will concentrate on the AFQ-Y. Employing a linear mixed effects model, analyses will incorporate a random intercept for the group (i.e., training group within institution), intervention as the fixed effect, and baseline scores as covariates. These exploratory analyses will present estimates with 95% confidence intervals, without correction for multiple testing, emphasizing their interpretative nature as potential signals.

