#### Plans for communicating important protocol amendments to relevant parties (e.g., trial participants, ethical committees) {25}

All amendments, substantial and non-substantial, will be submitted to the EKNZ and implemented only after obtaining the necessary approval. The study team will undergo training on the revised study protocol and all registries will be updated accordingly. In the event of any changes to the trial, affected participants will be notified, and efforts will be made to obtain their re-consent.

The following substantial amendments were made after the initial registration of the trial to enhance participant engagement and accommodate institutional constraints:

Amendments in June 2022:Revised procedures for quality assurance and trainer support.Revised exclusion criteria to prevent excessive exclusion of potential participants.Introduced participant reimbursement.Decreased the minimum number of participants per institution to 4 to enable participation of smaller institutions.Adjusted randomization timing to minimize waiting periods, facilitating more efficient planning of trainer and staff training sessions based on randomization conditions.Adding email addresses to participant consent to streamline staff workload and align with preferred contact methods.

Amendments in September 2022:

Intervention phase shortened from 12 to 9 weeks to accommodate varying participant lengths of stay.Facilitating participation for adolescents and institutions by allowing multiple consecutive or parallel groups within large institutions (same condition).Adjusted sample size to 150 due to smaller-than-expected group sizes in previous recruitment, with calculations based on groups of 4 participants.All materials were provided in French for the French-speaking part of Switzerland.

Amendments in August 2023:Individual expert interviews instead of group discussions for Trainer Satisfaction to accommodate resource constraints of some institutions and ensure their participation.

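### Institutions are randomised and may hold several training groups, but the models have a random intercept only for the group; if institutions differ and any holds more than one group, type I error exceeds 5%

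*Protocol article*

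**What the plan says.** **Unit of allocation.** Sequence generation {16a} says "The randomization process will occur at the institutional level", once at least four eligible participants are available. Implementation {16c} agrees, and the Discussion repeats that "150 AYA with a need to improve resilience will be randomly assigned at the institution level to one of three conditions".

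**Several groups per institution.** The September 2022 amendments listed in {25} include "allowing multiple consecutive or parallel groups within large institutions (same condition". Such groups share their institution's allocation and are not randomised separately.

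**Primary model.** Statistical methods {20a} specifies one random effect: "The identifier of the institution group will be included as a random intercept to account for the clustered data structure". The bracketed gloss that follows refers to participants in training groups nested in institutions.

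**Secondary models.** The same section says "analyses will incorporate a random intercept for the group (i.e., training group within institution".

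No passage describes an institution-level term. One further sentence in {16a} blurs the unit: "Participants will be randomized within fully eligible groups of 4 to 12 individuals, stratified by study site and across 3 conditions".

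**The concern.** In a cluster-randomised comparison, the variance of an arm contrast is set by how much the randomised units differ. Two groups in one institution share staff, climate and allocation. If the only random intercept is at group level, they enter as two independent allocations. The covariance between them is left out, and the standard error of every arm contrast is too small.

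Institution-level variance is plausible on the article's own terms. Secondary objectives lists institutional criteria among the covariates and potential moderators and plans to examine the institution's social atmosphere as a moderator. Social atmosphere is measured with its own questionnaire. In the self-help and TAU arms participants do not attend sessions together, so resemblance there is more naturally institutional than group-based.

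At stake are the p-values and 95% confidence intervals of a trial described as confirmatory. The per-protocol and available-case analyses in {20b} repeat the primary analysis and inherit the problem.

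**Working it through.** **Inputs from Sample size {14}:** rho 0.2 within a group, 4 participants per group, effective N 78 (26 per arm), drop-out 20%, total 150 (50 per arm). Alpha is not stated; two-sided 0.05 is assumed, from the 95% interval and the two-sided alternative.

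**The plan's own figure.** Design effect 1 + (4 − 1)(0.2) = 1.6. Then 78 × 1.6 = 124.8, and 124.8 × 1.2 = 149.8, that is 150. So 150 is reproduced with the group of 4 as the whole cluster and no institution level. (Dividing by 0.8 instead of multiplying by 1.2 would give 156.)

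**Closed form, every institution with two groups of 4.** Let rho_I be the part of the 0.2 that lies at institution level.
- Variance factor implied by the group-only model: 1 + 3(0.2) = 1.6.
- True factor: 1 + 3(0.2) + 4·rho_I.
- rho_I = 0.2: 2.4. The SE is too small by √(2.4/1.6) = 1.22, and type I error is 2[1 − Φ(1.96/1.22)] ≈ 11%.
- rho_I = 0.1: 2.0. The SE is too small by √(2.0/1.6) = 1.12, and type I error is about 8%.

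**Simulation.** 6,000 null data sets per scenario, 12 groups of 4 per arm (48, close to the planned 50), three arms, REML random-intercept model, t reference with clusters − 3 degrees of freedom. Entries are type I error of the group-only model, by how rho 0.2 is split between institution and group.

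| Institutions per arm | 0.2 / 0 | 0.1 / 0.1 | 0.05 / 0.15 | 0 / 0.2 |
|---|---|---|---|---|
| 12 with one group | 5.0% | 4.8% | 4.9% | 5.2% |
| 10 with one, 1 with two | 5.7% | 5.8% | 5.2% | 4.5% |
| 8 with one, 2 with two | 6.7% | 6.1% | 5.6% | 5.1% |
| 4 with one, 4 with two | 9.5% | 7.2% | 5.8% | 5.1% |
| 6 with two | 12.1% | 7.8% | 6.5% | 4.9% |
| 4 with three | 18.2% | 12.0% | 8.0% | 4.7% |

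The Monte Carlo standard error near 5% is √(0.05 × 0.95/6000) = 0.3 points, so the smallest excesses are barely distinguishable from nominal. With a normal reference the figures are about 1 point higher. A simpler simulation (t-test on group means, 22 degrees of freedom, 20,000 data sets per scenario, first two splits) gave 7–9%, 8–12% and 11–18% for the last three rows.

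**After the change.** With the random intercept at institution level and a t reference on institutions − 3 degrees of freedom, type I error was 4.0–5.4% in every scenario with institution variance above zero, and the model SE was 0.99–1.02 of the true value. The reference distribution matters: with four institutions of three groups per arm, the same model with a normal reference gave 7.2–8.0% in those scenarios.

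All simulations treat the outcome as already adjusted for baseline and use equal group sizes.

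**The case against.** **The inflation is conditional.** A reader might infer that the trial's type I error does exceed 5%. The article does not support that. The amendment only permits several groups, and only in large institutions. Other text points to small sites: the minimum was lowered to four participants so that smaller institutions could join, and groups of four were what was observed. With one group per institution the two models coincide. This stands, and it is why the result is given as a range starting at no inflation.

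**The correlation is borrowed.** The 0.2 is stated for participants in the same group. Placing half or all of it at institution level is an assumption. Adjustment for baseline AFQ-Y may also absorb part of any stable difference between institutions. This stands too, as the smaller figures in the 0.05 / 0.15 column show.

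**The wording may be loose.** The identifier's label in {20a} could be shorthand for a nested structure, and the statistical analysis plan, which is not shown, may spell that out. But the secondary text has "a random intercept for the group (i.e., training group within institution" as its single cluster term, and the article fixes the level itself. A statistician following it would fit group only.

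**Stratification.** A reader might also infer from {16a} that participants are randomised individually within groups, or that a stratification factor is missing from the model as a fixed effect. Neither is supported. The rest of the article makes the institution the unit. Study site is not defined, and if it means institution, a fixed effect for it would be confounded with arm. The sentence only needs reconciling with institution-level allocation.

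**Secondary endpoints** are declared exploratory, so the consequence there is lighter.

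**Conclusion.** The point holds in conditional form. As written, the models omit the level at which treatment is allocated, and no other passage supplies it. Given at least one multi-group institution and positive between-institution variance, the direction of the error is certain: standard errors too small, type I error above 5%.

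Its size is unknown. With rho 0.2 half or wholly at institution level it runs from under 2 points (one or two such institutions per arm) to 11–18% (all institutions with three groups). It is smaller if less of the correlation is institutional, and nil if each institution has one group or institution variance is zero. The scenarios are assumptions, not a description of the trial's data.

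**What to change.** In {20a}, and in the analysis plan that implements it:
- Specify a random intercept for institution, with training group nested within it where that variance can be estimated, and institution alone otherwise.
- Base tests and intervals on the number of institutions rather than the number of groups or participants.
- Use the same structure in the secondary models.

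In {16a}, reconcile the sentence on randomising participants within groups and stratifying by study site with institution-level allocation. Do not add a fixed effect for study site on the strength of that sentence.

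The cost is one model term and some wording; no new data are needed. Confidence intervals become somewhat wider: in the two-group case above by a factor of 1.12 to 1.22, before the effect of fewer degrees of freedom. If no institution ran more than one group, the institution-only model is the planned model and nothing is lost. If several groups were run but institutions do not differ, the institution-level test is at worst mildly conservative (3.5% in the most extreme scenario).
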